**Health-related quality of life**	
Amyotrophic Lateral Sclerosis Assessment Questionnaire (*ALSAQ-40*)	ALSAQ-40 score is a patient self-report health status PRO based on 40 questions specifically used to measure the subjective well-being of patients with ALS in a scale from 0 (best possible health status) to 100 (worst possible)
EQ-5D scale score (*EQ-5D-5L*)	The 5-level EQ-5D version is a self- assessed health-related quality of life (HRQoL) questionnaires based on 5 questions ranging from 0 (worst health) to 100 (best health)
**Biomarker**	
Creatinine level	Plasma creatinine is a breakdown product of creatine phosphate and it is related to muscle mass, expressed in μmol/L or micromol/L
Neurofilament level	Value of neurofilaments (light chain and phosphorylated heavy chain) in the CSF and serum resulting as a mean from triplicate measurements expressed in pg/ml
MMP-9 expression	The expression of matrix metalloproteinase-9 in serum is a mean of at least two duplicates, expressed in pg/ml

### Analysis method for primary and secondary outcomes

In the primary analysis, the effect of treatment on the primary endpoint will be measured by means of the odds ratio estimated through an unadjusted logistic regression model including a dummy variable for treatment group. Moreover, as part of the sensitivity analyses, a multivariable logistic regression model will be performed. Survival outcome will be analyzed using Kaplan–Meier survival analysis and log-rank test. Univariate and multivariable Cox proportional hazards models will also be applied. Additionally, the joint modeling omnibus test [13] will be used to assess the simultaneous effect on ALSFRS-R and survival. The longitudinal secondary endpoints (ALSFRS-R, ALSAQ-40, FVC, EQ-5D scale, MRC scale, and biomarkers) measured on a continuous scale will be analyzed using a multivariable linear mixed effect model (LME) to estimate the mean difference in the rate of decline between TUDCA and placebo over 18 months. The following covariates will be included in the multivariable models: age, gender, type of ALS, and region of initial site of diagnosis.

Country will be included as a random factor in the LME models. Clustered standard errors by country will be used in logistic and Cox regression models to obtain robust estimates. All primary and secondary analyses will be carried out on both ITT and per-protocol populations.

### Subgroup analyses

Exploratory subgroup analyses will be performed for the primary outcome in the ITT population, according to the following subgroup variables measured at randomization (month 0): site of onset, type of ALS (familial, sporadic), age (categorized according to the median), duration of the disease since symptom onset (categorized according to the median), gender, country. Moreover, an exploratory analysis will be conducted stratifying patients according to neurofilaments level [14]. The subgroup effect will be estimated including an interaction term for each subgroup variable at time in the logistic regression. The forest plot will be used to summarize subgroup analyses. The subgroup analyses will also be carried out for the change from baseline on ALSFRS-R by adding the treatment-subgroup interaction term in the MLE model.

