### Sample size

The study was powered to assess the potential benefit of TUDCA compared with placebo on the rate of progression, as measured by the ALS-FRS-R total score. The target number of participants was determined based on the expected proportion of responders. In the original planning, based on data from the phase II study [5], a sample size of 199 subjects per arm was calculated to detect a 10% difference between arms assuming a response rate of 10% in the placebo group. This sample size provides at least 80% power with a two-sided alpha of 5%. Considering a dropout rate of 10% at 18 months, a total sample size of 440 patients was planned. Such a sample size provides 83.3% power to detect a 13% absolute difference in survival (defined as death or respiratory insufficiency) between the two treatment groups, corresponding to a hazard ratio of 0.616, assuming an 18-month survival of 60% in the placebo group. However, due to the impact of the COVID-19 outbreak on recruitment [9], the enrolment was planned to be closed at 320 randomized patients. The reassessed sample size allows us to detect an absolute difference of 11% in the proportion of responders between the TUDCA and the placebo arms. It also provides a power of 80% to detect a 14% absolute difference in survival, corresponding to a hazard ratio of 0.58.

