## Statistical principles

Statistical significance will be determined by a two-sided *p*-value ≤ 0.05. Confidence intervals at the 95% level (95% CI) will be reported for all outcomes and measures of association (proportions, means, odds ratios and hazard ratios). Main analyses will be carried out on the intention-to-treat (ITT) population.

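### Age and disease duration are cut at the sample median before the treatment interaction is tested; if effect modification is graded, this gives up about 25% to 36% of the information on it

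*SAP article*

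**What the plan says.** The section on subgroup analyses sets the status and scope: "Exploratory subgroup analyses will be performed for the primary outcome in the ITT population". Two of the listed variables are continuous by nature and are reduced to two levels: "age (categorized according to the median), duration of the disease since symptom onset (categorized according to the median"). The test is described as follows: "The subgroup effect will be estimated including an interaction term for each subgroup variable at time in the logistic regression". I read this as a treatment-by-subgroup term, one variable at a time. The sentence on the second outcome supports that reading: "The subgroup analyses will also be carried out for the change from baseline on ALSFRS-R by adding the treatment-subgroup interaction term". A forest plot summarizes the results.

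The section describes no interaction test with age or duration kept continuous and gives no reason for the cut. The continuous values exist. Both variables are taken at month 0, and the section on baseline characteristics summarizes continuous data by mean, standard deviation and quantiles. Eligibility admits ages 18 to 80 and disease duration up to 18 months.

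**The concern.** A median cut treats everyone on one side of the median as alike and separates patients who sit just either side of it. If benefit changes gradually with age or with time since onset, most of that gradient lies within the halves, where the planned test cannot see it.

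Interaction power is already scarce here. The outcome is itself a dichotomy (responder or not), and enrolment was reduced from 440 to 320. At stake is whether these exploratory analyses can pick up a graded dependence on age or on how early treatment starts. The trial's main conclusion is not at stake.

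**Working it through.** **Inputs from the SAP article.** 1:1 allocation; 320 randomized; an 11-point detectable difference after the reassessment; two-sided 5% level ("Statistical significance will be determined by a two-sided *p*-value ≤ 0.05").

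**Assumptions, because the article is silent.** Placebo response stays at 10%, so 10% v 21% at the average modifier value; size and shape of the interaction; distribution of the modifier.

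**Step 1: the plan's own figure.** The article gives no interaction power, so the only anchor is the main effect: "a sample size of 199 subjects per arm was calculated to detect a 10% difference between arms assuming a response rate of 10"%. With pooled variance and p̄ = 0.15:

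n = [1.96·√(2·0.15·0.85) + 0.8416·√(0.10·0.90 + 0.20·0.80)]² / 0.10² = (0.990 + 0.421)² / 0.01 ≈ 199 per arm.

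This reproduces the plan. By the same method, 160 per arm and 10% v 21% give 77.9% main-effect power with no dropout.

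**Step 2: information kept by a median cut.** For a linear interaction, the relative efficiency is the squared correlation between the modifier and its above/below-median indicator.
- Normal modifier: 2/π = 0.637, so about 36% is lost.
- Uniform modifier: (√3/2)² = 0.75, so 25% is lost.

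**Step 3: what that does to power.** If the continuous test has noncentrality δ, its power is about Φ(δ − 1.96), and the cut multiplies δ by the square root of the efficiency. Take 50% power with continuous coding, so δ = 1.96:
- Normal: Φ(1.96·0.798 − 1.96) = Φ(−0.396) = 34.6%, a loss of 15.4 points.
- Uniform: Φ(1.96·0.866 − 1.96) = Φ(−0.263) = 39.6%, a loss of 10.4 points.

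**Step 4: simulation.** 320 patients; logistic model with treatment, modifier and their product; ordinary Wald test; 3000 trials per setting. Entries are power in %, continuous v median cut, with the loss in points in brackets (from unrounded rates).

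| Odds-ratio ratio per SD (log) | Normal | Uniform | Right-skewed (gamma, shape 4) |
|---|---|---|---|
| 1.25 (0.22) | 10.4 v 7.2 (3.3) | 10.2 v 8.4 (1.8) | 9.7 v 8.3 (1.5) |
| 1.5 (0.41) | 23.1 v 15.4 (7.7) | 21.9 v 17.1 (4.8) | 21.7 v 15.6 (6.1) |
| 1.75 (0.56) | 39.3 v 25.4 (13.9) | 37.1 v 28.5 (8.6) | 39.4 v 24.5 (14.9) |
| 2.0 (0.69) | 52.8 v 35.7 (17.1) | 54.5 v 42.8 (11.7) | 57.0 v 37.2 (19.8) |
| 2.5 (0.92) | 76.0 v 55.0 (20.9) | 74.9 v 60.9 (13.9) | 79.2 v 54.2 (25.0) |
| 3.0 (1.10) | 87.0 v 67.9 (19.1) | 88.0 v 75.9 (12.1) | 92.6 v 68.0 (24.6) |

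Separate runs at exactly 0.2 per SD gave losses of about 0 to 3 points. At 0.4 to 1.0 per SD they gave about 6 to 21 points (normal) and 6 to 14 (uniform).

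**Step 5: sensitivity.**
- Response rates of 25% v 36% with a normal modifier (2000 trials per setting): losses of 10 to 19 points at 0.4 to 1.0 per SD.
- True effect a step exactly at the median, odds-ratio ratio 2 to 6: the cut gains 4 to 20 points (normal) or 8 to 26 (skewed).

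**Step 6: how large these interactions are.** The central odds ratio is (0.21/0.79)/(0.10/0.90) = 2.39. At 1.0 per SD it runs from 2.39·e⁻¹ = 0.88 one SD below the mean to 2.39·e¹ = 6.5 one SD above. At 0.8 per SD it runs from 1.07 to 5.3. The largest losses therefore need an effect that vanishes or reverses about one SD from average.

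**The case against.** The strongest reply is that this is a matter of preference. The analyses are labelled exploratory, the variables and the cut rule are fixed in advance, and a pre-specified median split is a common convention that removes any later choice of cut point. Nothing in the section is contradictory. All of that stands, and it is why the point is only a cheap improvement. It does not remove the loss under a graded effect, and a pre-specified continuous term also leaves no cut point to choose.

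A reader might infer more than the article supports, in four ways:
- **A fixed power cost for this trial.** No interaction size, shape or modifier distribution is given. The loss is near zero for small interactions, and its sign reverses for a step at the median. A normal modifier is doubtful for duration, which eligibility caps at 18 months.
- **That the codings hold the planned type I error equally well.** The ordinary Wald tests above rejected in 4.7% (continuous) and 4.5% (cut) of null trials with a normal modifier. The analysis-method section, however, plans standard errors clustered by country in logistic models, and there are seven countries. A check with clustering, random country membership and no country effect gave about 11% and 9%. The point loss was similar, but the absolute rates above do not describe the planned test.
- **That the subgroups could not be used in another trial.** Once the numeric cut is reported, they can.
- **That a non-significant interaction will be reported as a consistent effect.** The section sets no such rule; it says only that the subgroup effect will be estimated.

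**Conclusion.** The point holds in a conditional form and is minor. The plan tests two continuous modifiers only after cutting them at the sample median. Under a smooth, roughly log-linear interaction this discards about 25% (uniform) to 36% (normal) of the information. With 320 patients, 10% v 21% responders and ordinary Wald tests, that means about 0 to 3 points of interaction power at 0.2 per SD and about 6 to 21 points at 0.4 to 1.0 per SD. The loss reached 25 points for a right-skewed modifier. The upper end belongs to very strong interactions. The cut is the better coding only if the true effect is a step near the median, a value set by who happened to enrol.

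Continuous coding would not make these tests well powered. In the simulations its power stayed below 80% up to an odds-ratio ratio of 2.5 per SD. No loss was computed for the ALSFRS-R mixed model. The primary analysis is untouched.

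**What to change.** In the section on subgroup analyses, replace the coding of these two variables along these lines: *Treatment-by-age and treatment-by-duration interactions will be tested with the modifier as a continuous term. A restricted cubic spline will be fitted as a check on linearity, and the estimated odds ratio will be plotted against the modifier. Median-split estimates will be shown in the forest plot for display only.* Use the same coding for the interaction terms in the ALSFRS-R mixed model.

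The cost is SAP wording and one changed model term in each analysis; no new data are needed and the planned forest plot is kept. The downside is a linearity assumption, which the spline checks. The change should be dated before unblinding; if it is made later, the continuous tests should be reported as post hoc.

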### Missing data

#### Imputation rules and key sensitivity analyses

In the primary analysis, for each patient, all available ALSFRS-R scores will be included in the linear regression model to estimate the monthly decline. The following rules for handling missing data will be applied: (i) for deceased patients, as death is clearly a poor outcome and there is no consensus on an alternative score, the lowest score (zero) will be assigned at the time of death, and (ii) for withdrawals or LTF patients without a post-randomization assessment of the ALSFRS-R score, the monthly decline of ALSFRS-R will be imputed using the “nearest neighbor” procedure [15]. For each of these subjects, we will identify the five other participants within the same treatment group whose baseline ALSFRS-R scores were closest to the baseline score of the patient. Then, the largest monthly ALSFRS-R decline observed among the identified neighbors (worst-case imputation) will be used for imputation. All missing data will be imputed within treatment groups defined by the randomized treatment assignment. As sensitivity analysis, within the nearest neighbor procedure, the “bestcase imputation” will also be carried out imputing the smallest observed monthly decline.

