## Analysis

### Outcomes

The primary outcome is measured through the identification of the responder patients, defined as those showing an improvement of at least 20% in the ALSFRS-R slope during the 18-month randomization period compared to the 3-month lead-in period. Slope coefficients for ALSFRS-R decline will be calculated separately for the lead-in period and the treatment period using the linear regression model.

The secondary efficacy outcomes are presented in Table 2. The safety and tolerability of TUDCA will be evaluated through the assessment of adverse events, concomitant treatments, physical examinations, vital signs, and routine laboratory tests (hematology and biochemistry).

**Table 2 Tab2:** Secondary and exploratory outcomes

Variable	Description

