**Clinical**	
ALSFRS-R score (*ALSFRS-R)*	ALS Functional Rating Scale Revised consists of 12 questions, each scored out of 4 points. A total score is calculated by summing the scores from each question with a maximum score of 48 (better performance, i.e., absence of the measured symptoms of ALS) and a minimum score of 0 (worst performance)
Survival time measured by death or respiratory insufficiency	Survival status is recorded at the end of study as well as respiratory insufficiency defined as tracheostomy or the use of non-invasive ventilation for ≥ 22 h per day for ≥ 10 consecutive days. Survival time is defined as the time elapsed between randomization and death from any cause and tracheostomy, whichever occurs first
Forced vital capacity score (FVC)	The index of respiratory function expressed as a percentage of the expected value is used to indicate potential respiratory compromise
Muscle force assessed by the Medical Research Council (MRC) scale	MRC score is a summation of the strength of 6 muscle groups tested on both sides ranging from 0 (paralysis) to 60 (normal strength)

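### The primary ALSFRS-R slope has no rule for scores at 0, so a patient whose decline never slows but who reaches 0 by about month 13 is classed as a responder

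*SAP article*

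**What the plan says.** The SAP article (Outcomes) defines responders as patients with an "improvement of at least 20% in the ALSFRS-R slope during the 18-month randomization period compared to the 3-month lead-in period". On the estimator it says: "Slope coefficients for ALSFRS-R decline will be calculated separately for the lead-in period and the treatment period using the linear regression model". Under Imputation rules and key sensitivity analyses it adds that, for each patient, "all available ALSFRS-R scores will be included in the linear regression model to estimate the monthly decline".

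That section has two special rules:
- For deceased patients, "the lowest score (zero) will be assigned at the time of death".
- For withdrawn or lost patients with no post-randomization score, "the largest monthly ALSFRS-R decline observed among the identified neighbors (worst-case imputation) will be used for imputation".

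Table 2 gives the scale as 0 to 48, with 0 the worst. It also has "respiratory insufficiency defined as tracheostomy or the use of non-invasive ventilation" above a stated duration, but only within the secondary survival outcome. No rule covers a patient whose observed score has reached 0 and can fall no further.

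**The concern.** Once a score is 0, every later visit adds another 0. The straight line then averages a steep fall and a flat stretch, and its slope understates how fast the patient declined. The lead-in line has no such flat stretch. The comparison can therefore show an improvement that comes only from the bound of the scale.

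The patients concerned have some of the worst courses in the trial, and their lead-in slope is steep and well defined. Labelling them as treatment successes runs against the plan's own view of death as a poor outcome, and it adds responders that carry no information about TUDCA.

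**Working it through.** **Inputs from the SAP article.** Visits at months 0, 3, ..., 18 (Trial design, Table 1). Responder if fitted treatment decline ≤ 0.80 × lead-in decline (Outcomes). Scale minimum 0 (Table 2). Zero at death (Imputation rules). 10% versus 20% responders, 199 per arm, two-sided 5%, 80% power (Sample size).

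**Assumed, because the article does not give them.** Month-0 scores and individual rates of decline. The lead-in slope is taken as measured without error, and the true rate never changes.

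**1. The plan's own figure.** With pooled variance and no continuity correction, n = [1.96 × √(2 × 0.15 × 0.85) + 0.8416 × √(0.09 + 0.16)]² / 0.10² = 199 per arm. The stated figure reproduces.

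**2. One patient.** Month-0 score 36, 3 points/month before and after randomization: 36, 27, 18, 9, 0, 0, 0.
- Mean visit time 9; Sxx = 81 + 36 + 9 + 0 + 9 + 36 + 81 = 252.
- Sxy = −9×36 − 6×27 − 3×18 = −540.
- Fitted decline 540/252 = 2.14; ratio 2.14/3 = 0.71. This is a responder at the 20% threshold and at the supporting 25% threshold.

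**3. The cut-off.** Let T be the month at which 0 is reached. For T between 12 and 15, Sxy divided by the rate is −[9T + 6(T−3) + 3(T−6) − 3(T−12)] = −15T, so the ratio is 15T/252. Setting it to 0.80 gives T = 13.44, whatever the start score. If month 0 is left out of the fit, the cut-off is month 14.2.

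| Month-0 score | Lead-in decline needed (score/13.44) |
|---|---|
| 24 | 1.79/month |
| 30 | 2.23/month |
| 36 | 2.68/month |

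With a score of 36:
- 2.5/month reaches 0 at month 14.4, ratio 0.857: not a responder.
- 2/month reaches 0 at month 18, ratio 1.00: not a responder.
- 4/month gives ratio 0.50: responder.

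The scale maximum of 48 also limits who can be affected. A constant decline through the lead-in needs score + 3 × rate ≤ 48, so at the cut-off score × (1 + 3/13.44) ≤ 48, a month-0 score of about 39 or less.

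**4. A bound.** If scores never rise and all visits are present, the steepest possible fit is a single drop from the start score B to 0 mid-period: 18B/252 = B/14. A lead-in decline of B/(14 × 0.80) = B/11.2 or more (3.21/month for B = 36) therefore guarantees response.

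**5. Death.** Score 36, 3/month, death at month 16: times 0, 3, 6, 9, 12, 15, 16 and scores 36, 27, 18, 9, 0, 0, 0.
- Sxy = 270 − 61×90/7 = −514.3; Sxx = 751 − 61²/7 = 219.4.
- Decline 2.34, ratio 0.78: responder.

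Other cases from 36:
- 3/month, death at month 14: ratio 0.91, non-responder.
- 4/month, death at month 12.5: ratio 0.73, responder.
- 1/month, death at month 16: ratio 1.66, non-responder.

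**6. Frequency, on assumptions only.** Log-normal decline with median 1.0 and log-SD 0.5 to 0.6 puts about 2.3% to 4.9% of patients above 2.7/month. If a fifth to a half of these are alive at month 18, that is about 0.5% to 2.4% of an arm, or roughly 1 to 4 of 160, against 16 placebo responders expected at 10%. Late deaths at the floor would add some. Other log-normal assumptions (mean 0.8 to 1.5/month, CV 0.6 to 0.7, month-0 score about 37) give about 1% to 11% before deaths are removed.

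**7. Dilution.** If a share f of true non-responders in each arm becomes false responders, the rates are 0.10 + 0.90f and 0.20 + 0.80f. Power at 199 per arm is 80.0% for f = 0, 77.4% for 1%, 74.8% for 2% and 67.2% for 5%.

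**The case against.** The case against accepts the arithmetic and attacks its reach. Most of it stands as a limit on the point.

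- A reader might infer that every fast decliner who ends at the bottom is a responder. Step 3 shows otherwise: after about month 13.4 the label is correct.
- A reader might infer that death is scored as failure and only survivors slip through. The plan has no such rule. Death adds one zero to the same regression, and step 5 shows it can leave a responder. Nor is death the only poor outcome handled, since patients lost without a post-randomization score get a worst-case slope.
- A reader might infer that tracheostomy or ventilation creates the false response. Nothing in the article says either puts the total at or near 0. They matter only because the primary rule is silent on them. Keeping them in the survival outcome, with a joint test of function and survival, is a defensible choice.
- A reader might infer bias in favour of TUDCA. The article gives no evidence of a difference between arms, and the frequency is assumed throughout.

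The mechanism itself is not answered. Multiple imputation addresses missing scores, not observed zeros. The 25% threshold, the covariate-adjusted model and the analysis relating responder status to survival all use the same slope rule. The mixed model and the joint test are secondary and do not change the label.

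**Conclusion.** The point holds in a limited form. A straight-line fit on a bounded scale, with no floor rule, classes a patient with unchanged decline as a responder when 0 is reached by about month 13.4, and a zero entered at a late death does not reliably prevent it. This follows from the plan's own rules, given a constant decline and complete visits.

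How many patients are affected cannot be judged from the document. The share is probably small. Its main effect would be a modest loss of contrast, about 2.6 power points at 199 per arm for each 1% of false responders at the low end of the range. A difference between arms is possible only if survival at the floor differs, and the article gives no evidence of that. Because this is the primary endpoint and the repair is cheap, the rule should be corrected.

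**What to change.** In the primary slope, use scores only up to and including the first score of 0, and drop later zeros, including a zero assigned at death after that point. Add a prespecified sensitivity analysis in which death or respiratory insufficiency, as defined in Table 2, before month 18 counts as non-response. Report the rule as now written alongside.

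**Check of the repair under constant decline.** Refitting up to the first 0 gives these ratios:
- T from 6 to 9: (T+1)/10
- T from 9 to 12: (T+3)/15
- T from 12 to 15: (T+6)/21
- T from 15 to 18: (T+10)/28

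All exceed 0.80 for any T after month 7, and both responder deaths in step 5 return to 1.00. A floor reached at month 7 or sooner can still pass, but from 36 that needs 36/7 = 5.1 points/month or more.

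Do not truncate at a patient's own lowest plateau above 0. Scores 36, 33, 33, 33, 33, 33, 33 after a lead-in of 1/month fit 27/252 = 0.11/month, a true stabilisation. Truncating at month 3 would give 1.0/month and a non-responder, and a patient with flat scores would have no slope at all.

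**Cost.** Two or three sentences in the SAP, using data already collected. A few patients lose responder status. Plateaus slightly above 0 produce the same artefact (from 36 with a plateau at 4, the cut-off is 32/13.44 = 2.38/month) and are covered only by the sensitivity analysis.

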#### Multiple imputation-based sensitivity analyses

We intend to calculate the post-randomization slope only after imputing missing ALSFRS-R data in the 18 months of treatment period and then categorize participants into responders/non-responders and finally conduct logistic regression analysis to estimate the effect of TUDCA. This approach is supported by simulation studies conducted by Floden and Bell [16]. A first sensitivity analysis will be carried out using the multiple imputation (MI) technique under the missing at random (MAR) assumption to deal with missing ALSFRS-R data. The imputation model will include the treatment group, the prognostic baseline characteristics, and ALSFRS-R at baseline. For patients deceased or withdrawn without a post-randomization assessment, the same rules specified for primary analysis will be applied. Moreover, the imputation of missing data under the missing not at random (MNAR) assumption considering the reason for missingness will be carried out using the delta-based MI method. A range of penalties by reason of missingness (study termination due to adverse events AE and death of patients) will be considered. All other missing data will be imputed under MAR assumption, applying a null penalty. For withdrawals without a post-randomization assessment, the same rules specified for primary analysis will be used. A total of 50 imputations for each analysis will be performed, which should provide adequate precision since the amount of missing data is not expected to be large [17]. Results from different imputed datasets will be combined using Rubin’s rule.

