#### Sensitivity analyses for handling missing data in the primary endpoint

Missing data are expected to increase during the trial due to the COVID-19 pandemic. In the primary and key sensitivity analyses, pandemic-related missing data will be treated as all the other missing data.

In these additional analyses, according to the estimand framework [19], the treatment policy strategy is adopted for COVID-19 intercurrent events. In such approach, we consider the pandemic irrelevant in the effect estimate, and all collected data are used in the analyses. All missing data will be imputed by MI under MAR assumption, by including also COVID-19 infection status and pandemic time-period in the imputation model [25]. Moreover, under the assumption that the pandemic (restrictive measures, lockdown and infections) could negatively affect the outcome, the analysis under MNAR assumption will be repeated, conducting a tipping point analysis for COVID-19-related missing data. MI analysis will be conducted using the number of imputations and the pooling rule previously specified.

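### For withdrawals with no follow-up score, the worst-case and best-case imputations move both arms the same way, and for those not related to COVID-19 no stated analysis tests an adverse difference between arms

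*SAP article*

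**What the plan says.** The rule is in the SAP article, section Imputation rules and key sensitivity analyses. It covers withdrawals and patients lost to follow-up who have no ALSFRS-R score after randomization.

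- **Donors:** "we will identify the five other participants within the same treatment group whose baseline ALSFRS-R scores were closest".
- **Primary analysis:** "the largest monthly ALSFRS-R decline observed among the identified neighbors (worst-case imputation) will be used for imputation".
- **Sensitivity analysis:** the same procedure "will also be carried out imputing the smallest observed monthly decline".
- **Scope:** "All missing data will be imputed within treatment groups defined by the randomized treatment assignment". No version treats the two arms differently.

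The section Multiple imputation-based sensitivity analyses then returns to these patients twice.

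- **Under MAR:** "For patients deceased or withdrawn without a post-randomization assessment, the same rules specified for primary analysis will be applied".
- **Under delta-based MNAR:** "For withdrawals without a post-randomization assessment, the same rules specified for primary analysis will be used". The penalties are defined by reason and not by arm: "A range of penalties by reason of missingness (study termination due to adverse events AE and death of patients) will be considered".

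The COVID-19 section on missing data in the primary endpoint says: "All missing data will be imputed by MI under MAR assumption, by including also COVID-19 infection status and pandemic time-period". It also repeats the MNAR analysis, with a tipping point limited to COVID-19-related missing data. It does not say whether patients without follow-up stay on the primary rule there.

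**The concern.** These are the patients whose responder status comes wholly from the imputation. A useful sensitivity analysis asks how unfavourable their unseen outcomes would have to be, in one arm relative to the other, before the conclusion changed. Switching both arms together from worst to best does not ask that.

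Same-arm donors add to the problem. If TUDCA donors respond more often, the best-of-five rule makes TUDCA withdrawals responders more often than placebo withdrawals, so the sensitivity analysis can widen a positive difference. The MNAR penalty for stopping because of an adverse event does not reach a patient who stops for that reason before the month 3 score.

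At stake is the robustness claim. A significant primary result could be reported as robust to missing data on the strength of analyses that could hardly have challenged it for this group.

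**Working it through.** **Inputs from the SAP (section Sample size).** Original plan: 10% placebo response, a 10-point difference, two-sided alpha 5%, 80% power, 199 per arm. Dropout: 10% at 18 months. Reassessment: 320 randomized (160 per arm at 1:1) and an 11-point detectable difference.

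**The plan's own figure.** Pooled-variance formula, no continuity correction:
n = [1.96·√(2·0.15·0.85) + 0.842·√(0.10·0.90 + 0.20·0.80)]² / 0.10² = 198.96, so 199 per arm. This reproduces.

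**Assumptions.**
- Observed response is 21% on TUDCA and 10% on placebo (the 10% carried over, plus 11 points).
- m patients per arm have no follow-up score. The SAP gives no number, so I use 3, 8 and 16. Sixteen is the whole 10% dropout (0.10 × 160) and so a ceiling.
- The five neighbours respond independently at their arm's rate p. Each patient's own lead-in slope, which also enters responder status, is not modelled.

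**Probability that an imputed patient counts as a responder.**
- Worst of five: p⁵, which is 0.0004 on TUDCA and 0.00001 on placebo.
- Best of five: 1 − (1 − p)⁵, which is 1 − 0.79⁵ = 0.692 on TUDCA and 1 − 0.90⁵ = 0.410 on placebo.

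**Expected proportion in an arm** = [(160 − m)·p + m·q] / 160, with q from the lines above. The p-value is from the pooled two-proportion z-test.

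**Worked case, m = 8, TUDCA worst with placebo best.**
- TUDCA: (152·0.21 + 8·0.0004)/160 = 19.95%.
- Placebo: (152·0.10 + 8·0.410)/160 = 11.55%.
- Difference 8.4 points; SE = √(0.1575·0.8425·2/160) = 0.0407; z = 2.06; p = 0.039.

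**Equal numbers in both arms (difference in points, p):**

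| m per arm | Worst/worst (primary) | Best/best (planned) | TUDCA worst, placebo best (not planned) |
|---|---|---|---|
| 3 | 10.8, p=0.007 | 11.3, p=0.006 | 10.0, p=0.013 |
| 8 | 10.5, p=0.008 | 11.9, p=0.005 | 8.4, p=0.039 |
| 16 | 9.9, p=0.011 | 12.7, p=0.004 | 5.8, p=0.16 |

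At 5 per arm the unplanned pairing gives 9.4 points (p=0.021), and at 10 per arm 7.8 points (p=0.057). Under the planned pair the odds ratio hardly moves: 2.36 v 2.31 at 16 per arm.

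**Unequal numbers.** With 16 TUDCA and 8 placebo patients the planned pair runs from 9.4 (worst) to 14.3 points (best). With 4 and 12 it runs from 11.2 (worst) to 9.9 (best). The opposite pairing still lies outside: 7.4 points (p=0.067) and 8.2 points (p=0.049).

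**All-or-none bound** (every TUDCA case a non-responder, every placebo case a responder; not the plan's donor rule): 8.9 points (p=0.03) at 3 per arm, 7.5 (p=0.07) at 5, 5.4 (p=0.20) at 8.

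**The case against.** **The group is narrow.** A patient must lack even the month 3 score, and telemedicine visits were available under the COVID-19 amendment. Later dropouts contribute the scores they have or enter multiple imputation. The 10% dropout covers all 18 months, and the SAP expects little missing data in general, although it also expects the pandemic to increase it. This stands, and it limits the weight of the point. At 3 per arm even the all-or-none bound stays significant.

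**The SAP does not call the two imputations bounds on the treatment effect.** True. The point is an improvement to the plan and does not correct a contradiction. The best-case run is nevertheless listed among the key sensitivity analyses, and for a positive result it can do little.

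**Other analyses exist.** The per-protocol analysis requires 80% of visits and would drop these patients. That is a different handling, but it does not stress the contrast.

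Three stronger readings are tempting and are not supported:

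- *Nothing in the plan stresses the difference for any of these patients.* The COVID-19 section imputes all missing data under MAR without restating the exemption, and adds a tipping point for COVID-19-related missing data. COVID-related cases may be reached. If the repeated MNAR analysis inherits the exemption, that analysis does not reach them. The text does not settle it.
- *The imputed responders cancel, so the difference cannot move.* It moves when withdrawal counts differ by arm, and even with equal counts best/best widens it.
- *A few early withdrawals would overturn the result.* Under the plan's donor rule significance goes only at about 10 per arm. Losing it at about 5 needs the all-or-none bound.

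**Conclusion.** The point holds for withdrawals and lost patients with no post-randomization score whose missingness is not COVID-related: the stated rules do not test an outcome that is worse on TUDCA and better on placebo. This reads the multiple-imputation exemption, which names withdrawals, as covering the lost-to-follow-up patients that the primary rule groups with them. For COVID-related cases the text is unclear.

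The size depends on a count that the SAP does not give. On the assumptions above, both planned versions stay significant throughout, while the opposite pairing costs at most about 1 point at 3 per arm (11.0 to 10.0) and about 5 points at the 16-per-arm ceiling (11.0 to 5.8). Because lead-in slopes are not modelled, these figures illustrate the mechanism and do not predict the trial's result. It is a cheap improvement worth making before unblinding.

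**What to change.** 1. Add two runs of the nearest-neighbour procedure: worst-case TUDCA with best-case placebo, and the reverse. Report both as bounds, beside the number of patients concerned in each arm.
2. Remove the exemption in the multiple-imputation section, so that these patients enter the delta-based and tipping-point analyses, with penalties that may differ by arm.
3. State in the COVID-19 section which rule applies to patients without any post-randomization score.

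The cost is two more runs of code the plan already needs, some further work on the delta-based analysis, and one clarifying sentence. The adverse pairing is conservative, so it should be labelled as an extreme and not read as a likely estimate.
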